## Abstract

**Background:**

People with neurodegenerative diseases may have difficulty learning new information, owing to their cognitive impairments. Teaching them techniques for learning in social contexts could alleviate this difficulty. The present study will examine the performances of patients with Alzheimer’s disease and patients with the semantic variant of primary progressive aphasia on a memory test administered in three social contexts. The protocol will make it possible to identify determinants of social interactions, social abilities, cognition, and personality that can explain the potentially beneficial effect of social context on learning in these patients.

**Methods:**

Thirty dyads (patient with primary memory impairment who meets criteria for Alzheimer’s disease paired with caregiver), 16 dyads (patient meeting criteria for semantic variant of primary progressive aphasia paired with caregiver), and 46 dyads (healthy controls with no cognitive complaints) will be recruited. A nonverbal memory test (social memory task) will be administered to each dyad in three different social contexts (presence-only, observation, collaboration). Patients and healthy controls will also undergo a neuropsychological assessment to measure social (interactions and abilities), cognitive and personality aspects. Patients will be compared with controls on differential social scores calculated between the presence-only and collaboration contexts, and between the presence-only and observation contexts. A multiple comparative case study will be conducted to identify social, cognitive and personality variables that potentially explain the differential scores in the collaboration and observation contexts.

**Discussion:**

For the first time, memory will be assessed in patients with Alzheimer’s disease and patients with the semantic variant of primary progressive aphasia in three different contexts (presence-only, observation, collaboration). The multiple comparative case study will make it possible to identify the determinants of memory performance in the social context, in order to create the most beneficial learning context for individual patients, according to their profile.

**Trial registration:**

This study was approved by the Ile de France XI institutional review board (2022-A00198-35), and registered on ClinicalTrials.gov (no. NCT05800028), on April 27, 2023.

## Background

Neurodegenerative diseases place patients in situations of dependence in which they have to interact with people who are often new to them and adapt to new living environments. These life changes involve learning and memorizing new information, which is particularly difficult for people with cognitive disorders, such as memory impairment in Alzheimer’s disease (AD) and language deficits in the semantic variant of primary progressive aphasia (svPPA). The amnesic form of AD, characterized by an initial and predominant memory disorder, is the commonest and most typical form of the disease [1]. Severe deficits in learning new information are a core feature of AD, although deficits in storage and retrieval cannot be excluded [2, 3]. A progressive loss of semantic knowledge is observed in svPPA [4]. The latter is characterized by an initial and predominant impairment of language, with poor verbal comprehension and profound word-finding difficulties that interfere with daily activities and include the impairment of confrontation naming and single-word comprehension. Current and proposed classifications suggest that svPPA and semantic behavioural variant frontotemporal dementia [5] are both early forms of semantic dementia. The latter is characterized by a gradual loss of semantic knowledge evidenced by difficulty finding words and identification deficits for objects and/or persons, and impaired word comprehension [6, 7].

Different learning techniques have been developed to try to compensate for the learning and memory deficits of patients with AD, or improve the naming and use of objects for patients with svPPA, in order to maintain their autonomy. *Errorless learning* acts on the encoding phase, the aim being to avoid learning incorrect information [8–11]. The *vanishing cues method* facilitates the retrieval of information by providing cues that gradually disappear [12, 13]. The purpose of *space retrieval* is to improve long-term retention through the repetition of learning with increasingly long intervals between the encoding of information and its retrieval [14, 15]. In patients with svPPA, the semantic features of concepts are enriched [16, 17], and object use is relearned [18].

All these techniques involve the creation of materials for each learning event and require numerous repetitions, but they do not always have observable long-term effects, and generalization to other types of material is not always effective or tested [19]. For patients with PPA, the most beneficial strategy is functional communication, where communication strategies that are already used by the patient are practised with a communication partner [20]. However, this and other similar techniques need to be performed with others, and cannot be practised alone.

Numerous social psychology studies among healthy individuals have shown that the *presence of others* can have, either a positive effect on cognitive performance (i.e., *social facilitation*) or a negative effect, (i.e., *social inhibition*). In memory tasks, both social facilitation and inhibition depend, on memory consolidation [21]: if learning is not consolidated, the presence of others during encoding has a negative impact on learning speed. Although there have been relatively few studies of memory tasks, results suggest that the social effect differs according to recall interval. While short-term recall (2 min) is impaired when individuals are observed during encoding [22], their performance improves as the time between encoding and recall increases (i.e., 15 min [23], and 45 min [22]). By contrast, when individuals are observed during a neuropsychological assessment, their cognitive performance decreases (i.e., social inhibition), with attention and memory tasks (immediate and delayed recall) being most negatively affected [24]. The nature of the social effect (i.e., facilitation vs. inhibition) may also depend on the real or perceived difficulty of the task [25], as well as on the individual’s assessment of the other person [26] or of the context in general. In other words, depending on the individual’s personality traits, assessment of the context, and feelings towards the task, learning in the presence of others may generate pressure through apprehension of the task and the fact of having to tackle its difficulties alone.

This pressure may be alleviated and cognitive load reduced in a context where individuals can observe someone else carrying out the task, insofar as they no longer have to tackle it themselves. *Observational learning* (i.e., receiving information, then using it) builds habits and improves observers’ skills [27]. However, although observational learning is advantageous because it avoids the cost of trial-and-error learning, individuals need to be selective, only using the relevant information that comes from learning from others [28, 29]. Observational learning of a motor sequence seems to be efficient in patients with AD [30].

Collaborative learning, through partners’ co-construction of ideas within what can be regarded as a particular memory group [31], is more effective than learning on one’s own [32]. *Collaborative learning* is defined as interaction between peers with the aim of jointly performing a task, and meets three criteria: communication, reciprocity, and common goal [33]. Collaboration is said to be beneficial for learning [34], and contributes to participants’ social, emotional and psychological wellbeing (e.g., collaborative learning at university [35]). However, collaboration may have some disadvantages, such as the possible dilution of motivation, decreased productivity if there are uneven contributions from members, and possible encoding of errors produced by collaborators and played back in subsequent recall [32]. Collaborative learning outperforms learning alone, both among older people undergoing the normal age-related deterioration in memory [36] and among patients with AD [37, 38]. The social dimension, including common idea building and conversational skills, therefore seems to constitute a favourable learning environment. Using a collaborative trial in which patients self-generated labels with a familiar partner, Duff and colleagues [37] showed that patients with AD can perform comparably to healthy individuals. Beyond their ability to build a common representation with their partner, patients with AD are capable of knowing that other people do not share this representation [39]. However, the mechanisms behind this effect are still poorly understood, given that these patients have impaired theory of mind (ToM; i.e., ability to attribute mental states to others) [40], an essential skill for acting appropriately in social exchanges. The presence of a social context may help to compensate for patients’ apparent difficulty constructing representations of others’ mental states [41]. Several neurological diseases are characterized by ToM disorders [42]. In semantic dementia, for instance, both cognitive and affective forms of ToM are affected [43], mainly as a result of right anterior temporal atrophy in the early stage of disease [5] or after bilateralization. Atrophy of the right anterior temporal lobe is correlated with impaired emotion recognition and person identification [5, 44–46]. Some patients may exhibit egocentric behaviour [47], and respond with their own personal preferences when judging the preferences of others [42]. These social behavioural disorders can be attributed to the ToM impairment reported in these patients [43], as well as to the impairment of semantic knowledge about social norms [42].

The main objective of the present study will be to assess whether social context (collaboration or observation) improves the memory performances of patients with a neurodegenerative disease who exhibit social cognition, memory or language disorders. A secondary objective will be to identify social (interactions and abilities), cognitive and personality variables that could explain differences in patients’ performances between collaborative and observation contexts.

To this end, a nonverbal memory test (social memory task) will for the first time be administered in three different social contexts (presence-only, observation, collaboration), to patients with AD, patients with svPPA, and healthy older people with no cognitive disorders. Participants will also undergo a neuropsychological assessment probing social (interactions and abilities), cognitive and personality aspects.

A multiple comparative case study will be conducted [48–50] to identify variables (social interactions and social abilities, cognitive skills, and personality traits) that could explain better performances in a collaboration or observation context than in a presence-only context.

## Methods

### Participants

We will recruit 184 participants in order to create 92 dyads: 30 dyads in which a person who meets the criteria for AD with primary memory impairment [1] is paired with a caregiver, 16 dyads in which a person who meets the criteria for svPPA [4] is paired with a caregiver, and 46 pairs of healthy controls with no cognitive complaints (HC).

The dyad partners must have socialized together for at least 2 h per week for at least 5 years. Patients and HC must be aged 50–85 years. Patients’ caregivers and HC must have no cognitive complaints and a Montreal Cognitive Assessment (MoCA) [51] score > 25.

Exclusion criteria for all participants will be (1) concurrent participation in a therapeutic drug trial, (2) prior neurological disorders (stroke, epilepsy, head injury with loss of consciousness lasting more than 1 h), (3) chronic alcoholism or drug addiction, (4) a clinically severe major psychiatric disorder within the previous 10 years, and (5) use of psychotropic medication.

The size of the patient groups was determined according to the feasibility of including this type of patient, based on studies carried out for more than 15 years in our research unit [43, 52, 53]. The size of the HC group was determined in relation to the size of the patient groups. To ensure that HC are not cognitively impaired, a quick cognitive test will be performed at the beginning of the psychological interview. Individuals who perform below the normal range will be excluded from the study and replaced.

### Social memory task

The social memory task takes the form of a game, and has been specially designed to be feasible in different social contexts and adapted to patients with cognitive disorders. The game consists in constructing 12 pairs of pictures by selecting a picture in a draw pile (always visible) and finding the same picture in a 12-box grid (hidden face; see Fig. 1). Participants (here, either patients or HC) are instructed to memorize the position of that match in the grid, as this will be tested later. A recall phase takes place 20 min after this learning phase. The game will be repeated in each of the three social contexts (presence-only, observation, collaboration; see “Procedure for social memory task” subsection below), with three different sets of pictures.

**Fig. 1 Fig1:**
[figure not shown]
Screenshot showing learning phase of social memory task, displayed on touchscreen of computer

This test will be displayed on the touchscreen of a computer with a detachable keyboard. The 12.3-inch touchscreen will lie flat on the table for the duration of the test. The material used for this task was taken from Snodgrass and Vanderwart’s set of object pictures [54]. These images were improved with colour and texture [55], and ranked according to familiarity and image agreement. We selected the first 72 pictures, and randomly assigned them to one of the three contexts (i.e., 24 pictures per context). There were therefore 12 target pictures and 12 distractor pictures for each context. This task comes in two phases: picture location learning, and location recall.

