#### Procedure for social memory task

The learning phase will take place in three social contexts: (1) *presence-only* context, where the participant performs the task alone, with the dyadic partner present in the same room but behind a screen; (2) *observation* context, where the participant observes the dyadic partner performing the task; and (3) *collaboration* context, where the participant and the dyadic partner perform the task together. Each dyad will perform the task in all three contexts. The order of the three contexts will be randomly counterbalanced across the dyads.

During the learning phase, regardless of the context (presence-only, observation, or collaboration), the participant, dyadic partner, and experimenter will all be present in the room (see Fig. 2 for room layout). The tables of the two members of the dyad will be placed side by side facing a wall, and the experimenter’s desk will be perpendicular to these two tables, more than 1 m away. In the presence-only context, the touchscreen will be placed between the participant’s table and the dyadic partner’s table. The dyadic partner will complete a questionnaire during this learning phase. In the observation and collaboration contexts, the dyadic members’ tables will be fixed together, and the touchscreen will be placed in the middle.

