#### Outcome of social memory task

For the learning phase, and for each social context, several scores will be collected: the number of trials performed before all the pairs of pictures are found, the number of clicks on each picture on the lefthand side of the screen, and on each picture in the grid. We will examine whether these scores are related to delayed recall performance, to establish whether a picture is remembered better and more accurately located if it has been seen several times.

For the picture recognition in the recall phase, we will record the numbers of correct responses (i.e., saying “yes” when the picture has previously been seen, and saying “no” when the picture has not been seen before) for each social context.

Finally, for the location recall, we will calculate an overall score for each social context. If a picture is correctly located in the grid, 1 point will be awarded, and if it is located in an adjacent box, 0.5 point will be awarded. If not, 0 point will be awarded.

We will assess whether social context influences the picture recognition and location recall scores, and use these scores to identify factors that could explain potential differences in recognition performance between social learning contexts.

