### Data analysis plan

Each participant’s performance in the presence-only context will serve as a reference score, and a differential score will be calculated by subtracting this reference score from the participant’s memory performance in the collaboration context. The *z* score of this differential score will then be calculated, based on the mean and standard deviation for the HC group. This will show whether each patient’s differential score differs significantly from that of the HC group. The same analyses will then be carried out for performance in the observation context.

As this study is designed to identify determinants (social interactions and abilities, cognitive skills, and personality traits) that could explain the differential scores for the collaboration and observation contexts, we will carry out multiple comparative case analyses [48–50], based on the differential scores for the collaboration context of at least three patients whose memory performance is substantially better in the collaboration condition, compared with the presence only condition, and for three patients whose performance is only minimally better. These six patients will be compared on their social skills (social interactions and abilities), personality (especially the cooperation and determination dimensions), and memory performance in classic neuropsychological tests. Following a logic of replication, other patients will be added to the analyses, to see whether a regular pattern emerges. The same analyses will be conducted on differential scores for the observation context.

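### As written, each social context has its own fixed picture set, so the raw gain over presence-only mixes the context effect with set difficulty; the z score against controls escapes this only if the set effect is equal in both groups.

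*Protocol article*

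**What the plan says.** Protocol article, Social memory task: the game is played once per context, "with three different sets of pictures". The material comes from a picture bank "ranked according to familiarity and image agreement". The top 72 pictures were taken, and the authors "randomly assigned them to one of the three contexts (i.e., 24 pictures per context". The text continues: "There were therefore 12 target pictures and 12 distractor pictures for each context". All of this is in the past tense and describes one completed split.

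Procedure for social memory task: "Each dyad will perform the task in all three contexts", and "The order of the three contexts will be randomly counterbalanced across the dyads". The Fig. 3 caption repeats that it is the order of contexts that is counterbalanced. The article does not describe rotating the sets over contexts, matching them, or piloting them for equal difficulty.

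Data analysis plan: presence-only performance is the reference, and "a differential score will be calculated by subtracting this reference score" from the collaboration score, then likewise for observation. Each patient's differential becomes a z score on the control mean and SD. Case analyses then contrast patients with large and minimal gains over presence-only.

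**The concern.** The subtraction always sets a score on one group of pictures against a score on another. If the collaboration pictures happen to be easier to remember or locate than the presence-only pictures, every dyad shows an apparent benefit of collaboration, whatever the order of contexts.

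Random allocation makes the sets equal in expectation. It was done once, however, so any chance imbalance is a constant shared by all 92 dyads and is not averaged out.

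Three readings are at stake:
- The main objective in the Background, which asks whether collaboration or observation improves patients' memory. That is a within-patient gain.
- The controls' own gain from social context.
- Any absolute statement that a patient gains a lot, or that one context is best for that patient, which is an aim stated in the Discussion.

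**Working it through.** **1. The article's own counts.** 72 / 3 = 24 = 12 + 12 pictures per context. 30 + 16 + 46 = 92 dyads, and 2 × 92 = 184 participants. These agree. There is no power calculation to reproduce, because the patient group sizes rest on feasibility.

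**2. What the differential estimates.** Write C for the context effect, S for the mean score on a picture set, and 0 for presence-only. With one set per context,

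E[differential for context c] = (C_c − C_0) + (S_c − S_0).

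Counterbalancing removes an average order effect. The term D = S_c − S_0 is the same in every order and for every dyad, so it stays.

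**3. Possible size of D.** Location recall is scored per picture ("If a picture is correctly located in the grid, 1 point will be awarded", half a point for an adjacent box, otherwise nothing), so 12 targets give a range of 0–12. Let s be the between-picture SD in recall probability (with partial credit, in expected points per picture). The documents do not give s, so a range is assumed. For one random split,

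SD(D) = 12 × s × √(1/12 + 1/12).

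| Assumed s | SD(D), location score 0–12 | P(absolute D > 0.5 point) |
|---|---|---|
| 0.05 | 12 × 0.05 × 0.408 = 0.24 | 4% |
| 0.10 | 12 × 0.10 × 0.408 = 0.49 | 31% |
| 0.15 | 12 × 0.15 × 0.408 = 0.73 | 50% |

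The number of participants does not enter the formula. For recognition, scored over 24 pictures, 24 × s × √(2/24) gives 0.35, 0.69 and 1.04 points.

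**4. Effect on the planned z score.** Suppose controls carry the full D and patients carry k × D. The bias in the mean patient z is (k − 1) × D / SD_HC, where SD_HC is the control SD of the differential (assumed 2 to 3 points, not given).
- k = 1 (equal in both groups): bias exactly 0.
- k = 0.5: for D of one SD, 0.5 × 0.245 / 3 = 0.04 up to 0.5 × 0.735 / 2 = 0.18.
- k = 0: 0.245 / 3 = 0.08 up to 0.735 / 2 = 0.37.

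**5. Does rotation help?** A simulation used 30 patients and 46 controls, no context effect, all-or-none scoring and an assumed item SD of 0.5 logit. The SD of the mean patient differential around its true value of zero was 0.66 points with fixed sets and 0.40 with sets rotated over contexts. The SD of the mean patient z was 0.25 and 0.24. Rotation therefore mainly improves the raw gain; the z score had little to lose under these assumptions.

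**The case against.** The strongest reply is that the planned analysis is not a test of raw gain. Each patient is placed against controls who saw the same pictures in the same contexts, so an additive set difference common to both groups cancels exactly. This stands, and it limits the point considerably. It does not cover the main objective, because a z score shows whether a patient's gain differs from that of controls, not whether the patient gained.

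Four stronger readings are tempting, and the documents do not support them:
- **Distorted case selection.** A shift common to all patients leaves their ranking within one contrast unchanged, and no absolute cut-off is stated. Only a patient-specific set effect, or an absolute reading of the gain, would matter.
- **A known inflation of the false-positive rate.** With 46 pooled patients and a differential SD of 2.5 points, a 5% test of mean gain against zero would reject about 10%, 24% or 38% of the time for the three values of s. The arithmetic is right, but both SDs are assumed and the article plans no such test.
- **Non-cancellation because controls are at ceiling.** No control or pilot scores are given. What the Background does report is loss of semantic knowledge in svPPA, with object identification deficits in semantic dementia. That makes equal set effects uncertain for object pictures but does not show that they differ.
- **Certainty that sets never rotate.** The article does not expressly exclude rotation. The plain wording nevertheless assigns pictures to contexts, and it mentions counterbalancing only for order.

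Two further replies carry some weight. Choosing the highest-ranked pictures probably narrows the spread in difficulty, which favours the lower end of the range for s. Rotation also has a price in a case-level design: each person's raw differential then contains that person's own set contrast, which could reorder patients and widen the control SD unless it is removed.

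**Conclusion.** The point holds in a limited form. On the plain text, context and picture set are fully aliased in the raw differential, and neither order balancing nor sample size removes the set term. The within-patient gain named in the main objective, the controls' gain, and absolute statements about a patient's gain or best context cannot be separated from set difficulty.

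The patient-versus-control z score is unbiased if the set effect is additive and equal in both groups. If it is not, a typical bias in the mean z is about 0.04 to 0.37 under the assumptions above. Ranking within one contrast is unaffected by a common shift.

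The actual imbalance is unknown and may be small. An SD of 0.24 to 0.73 points for the chance difference rests wholly on the assumed s of 0.05 to 0.15.

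**What to change.** State whether the sets rotate. If they do not:
- Rotate the three sets over the three contexts using three rotations, balanced as nearly as possible within each group (AD 10/10/10, svPPA 5/5/6, controls 15/15/16) and across context orders. A full crossing of 3 rotations with 6 orders needs 18 sequences. It is unnecessary, and 16 svPPA dyads could not fill it.
- Estimate set effects, for example from controls, and compute differential and z scores after removing them. Without this step, individual scores carry each person's own set contrast.
- If some dyads are already tested, rotate for the rest and adjust for set.
- If testing is complete, limit conclusions to the patient-versus-control contrast, and state that the raw within-patient gain cannot be separated from set difficulty.

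The cost is a changed stimulus allocation table, an added set adjustment, and slight extra noise in individual scores from estimating the set effects. No further participants or visits are needed. Set effects taken from controls would not fully correct svPPA scores if difficulty differs in that group, and the report should say so.
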